### Intervention Procedures

The participant workbook will be used to structure the order of intervention topics for each telecoaching session (Textbox 1). Participants will be encouraged to commence with a focus on healthy eating, as there is strong evidence to support dietary interventions for moderating pregnancy weight gain [33,34]. However, the intervention is tailored to meet individual participant’s needs and motivations.

In the telephone-delivered program, the calls are structured into three phases (Multimedia Appendix 2), with weekly, biweekly, and then monthly phone calls. Frequent contact at the beginning of the program provides more intensive support for behavior change from the outset. Less frequent contact in the latter part of the program facilitates participants’ autonomy and confidence in consolidating and maintaining lifestyle changes such that they will (optimally) become lifelong habits.

### Usual Care

The retrospective group was provided with traditional, unstructured face-to-face dietetic care. Women were offered individual appointments with the dietitian in a dedicated clinic within the maternity outpatient department. An initial appointment was booked for 40 minutes, with review appointments allocated 20 minutes. There was no guarantee of the same dietitian at each review appointment, and review appointments were booked based on clinical judgment in negotiation with the woman. No specified educational content or strategies were provided.

### Data Collection

Data will be collected by study-trained dietitian research assistants. Research Electronic Data Capture (REDCap), a secure online survey and data capture tool, will be used to record details of each telephone counselling session including progress, clinical information, and fidelity to the call procedures and topics. Routinely collected maternal and infant data will be accessed from medical records.

#### Primary and Secondary Outcomes

Outcomes are shown in Table 1 along with corresponding RE-AIM indicators and assessment tools. Details of validated tools to be used are provided below. Primary outcomes will include referrals and referral sources, uptake among eligible patients, withdrawal rates and reasons (where available), completion rates, average number of calls per participant, average length of calls per participant, completion of pre-post program assessments, staff and participant satisfaction, and program delivery costs. Secondary outcomes will include routinely collected delivery and pregnancy outcomes as well as patient-reported outcomes collected via online questionnaires at the commencement and completion of the program (anthropometrics, and behavioral and psychosocial factors). If a participant does not complete these assessments online, a follow-up telephone call will be completed by study staff to gather information via the telephone.

**Table 1 table1:** Primary and secondary outcomes, assessment tools, and RE-AIM (Reach, Effectiveness, Adoption, Implementation, and Maintenance) framework indicators.

RE-AIM indicator and description of outcome					Collection method/assessment tools
**Reach and representativeness (primary outcome)**					
	Percentage of eligible women referred			Administrative data	
	Percentage of referred women taking up the service			Administrative data	
	Number of sessions attended			LWdP^a^ program REDCap^b^ database	
	Participant characteristics			LWdP program REDCap database	
**Implementation (primary outcome)**					
	Completion of pre- and postprogram assessments			Questionnaires	
	Staff survey			Questionnaires	
	Completion rates			LWdP program REDCap database	
	Withdrawal rates			Medical records and LWdP program REDCap database	
	Reasons for withdrawal			Questionnaire	
	Coaching call fidelity			Self-assessment database	
	Interventionist characteristics and allocated participants			Staff administrative database	
	Implementation strategies			Mapped to Expert Recommendations for Implementing Change (ERIC) strategies [35]	
**Adoption and maintenance (primary outcome)**					
	Referral source and number of referrals			Medical records and administrative data	
	Staff survey			Questionnaire	
	Adherence to implementation protocol			LWdP program REDCap database	
**Effectiveness (secondary outcome)**					
	Anthropometric outcomes				
		Weight, height, BMI	Medical records and self-reports		
		Gestational weight gain	Medical records, classified according to Institute of Medicine recommendations [2] (adjusted to 36 weeks)		
	Behavioral outcomes				
		Dietary intake	Fat and fiber behavior questionnaire [36]		
		Physical activity	Active Australia Survey [37]		
		Sedentary behavior	International Physical Activity Questionnaire [38]		
	Psychosocial outcomes			Intuitive eating scale [39]	
	Delivery and pregnancy outcomes				
		Gestational diabetes mellitus (diagnosed according to the Queensland Health Clinical Guideline for Gestational diabetes mellitus [40]); pregnancy-induced hypertension (excluding pre-eclampsia and HELLP); pre-eclampsia; mode of delivery; delivery complications; birth weight: macrosomia (>4000 g) and large for gestational age (>90th percentile based on Australian population [41]); neonatal morbidity, treatment, and admission to special or intensive care	Medical records		
	Participant satisfaction			Semiquantitative survey	
	Staff satisfaction			Semiquantitative survey	
	Cost			Hospital financial and outcome records	

^a^LWdP: Living Well during Pregnancy.

^b^REDCap: Research Electronic Data Capture.

#### Withdrawal Rates and Reasons

Women who withdraw from the program after receiving at least one coaching call will be sent a text message with a link to a short electronic survey. This anonymous survey will evaluate satisfaction with the program and reasons for program withdrawal.

#### Staff Survey

The understanding and acceptability of the program by staff (including clinicians and administrative personnel) will be assessed via a survey 2 months prior to completion of the evaluation period. Both electronic and paper-based surveys will be available. Electronic links to the online survey will be disseminated to staff from line managers. Paper-based surveys will be available in staff lunchrooms with collection boxes available for return of the survey. Administrative staff will be asked about referral and booking processes, whereas clinicians will be asked about their referral practices, program understanding, and barriers to referral. Survey responses will be provided on a 5-point Likert scale.

#### Dietary Intake and Behavior

The fat and fiber behavior questionnaire (FFBQ) is a 20-item questionnaire used to assess dietary behaviors (frequency of consumption, use of food items, and food categories) that has been validated against a food frequency questionnaire in the adult Australian population and is able to detect changes in fiber and fat-related intake behaviors [36]. It provides information on general food patterns rather than specific energy and macronutrient intake. Nine items relate to the frequency of consumption of particular high-fat or high-fiber foods, measured on a 5-point Likert scale (ranging from 5=never to 1=6 or more days per week). Nine items ask about behaviors related to cooking, eating, or choosing foods, such as type of dairy products or bread, measured on a 5-point Likert scale (ranging from 1=never to 5=always) with a “not applicable or do not know” option for those who do not eat a particular food or are not aware of specific cooking methods [36]. Two items assess the number of servings of fruits (1 item) and vegetables (1 item) consumed each day [36]. These 2 items contribute to the fiber and total FFBQ scores and are also valid stand-alone measures of fruit and vegetable intake [42]. The FFBQ is easy to score and administer, provides a good alternative to food frequency questionnaires in interventions, and has been used previously with pregnant women [20].

The Intuitive Eating Scale-2 is a 23-item tool that measures individuals’ tendency to follow their physical hunger and satiety cues when determining when, what, and how much to eat [39]. Participants select the option that best describes their attitude or behavior to each item rated on a 5-point Likert scale (ranging from 1=strongly disagree to 5=strongly agree).

#### Physical Activity and Sedentary Behavior

The Active Australia Survey consists of 8 questions designed to assess the frequency and duration of walking and performing moderate and vigorous physical activity in the past week [37]. The total number of sessions and minutes of physical activity will be treated as continuous variables. Values greater than 840 minutes will be recoded to this value to avoid over-reporting in accordance with recommendations for use of survey items [23]. A single item from the International Physical Activity Questionnaire [38] will assess sedentary time. This item assesses the total duration of sitting time on a weekday in the past 7 days [38]. These questionnaires will all be administered electronically and verified by the dietitian.

#### GWG

Pregnancy weight data have been collected routinely at the study hospital since 2015. GWG will be calculated by subtracting self-reported prepregnancy weight from weight recorded at 36 weeks’ gestation [43]. Self-reported prepregnancy weight has been demonstrated to be an accurate depiction of weight at conception for most women [44]. For women who deliver prior to their 36-week appointment, the last recorded weight will be used to estimate GWG and will be adjusted for in multiple variable analysis. GWG will be categorized as inadequate, within range, or excessive according to prepregnancy BMI ranges recommended by the IOM [2] and adjusted for the 36-week measure.

### Analysis

#### Economic Evaluation

An economic analysis from a health services perspective will be conducted following the International Society for Pharmacoeconomics and Outcomes Research (ISPOR) guidelines for modeling [45]. The fixed costs of implementing the LWdP program (ie, expenditures required to deliver the program and train dietitians in health coaching) will be documented. Dollar values will be assigned to these resources using publicly available information such as appropriate salary rates for the time of personnel involved in the above activities and commercial costs for the production of any training materials and program booklets. Fixed costs will be allocated equally over all participants who consented to participate in the program. Variable costs (ie, those that are proportional to the volume of service provided) will be allocated in proportion to the stage of the program reached by individuals [46].

The costs of different birth outcomes will be determined from the Royal Brisbane and Women’s Hospital’s unit costing based on the previous 12 months of administrative data covering all births occurring in this time frame. Costs will be stratified by BMI category and gestational diabetes status. As cost data of this nature generally have asymmetric distributions and heteroskedastic errors [47], an appropriate statistical model (eg, generalized linear model, generalized linear mixed model, or generalized estimating equation) for comparing the costs of birth by gestational diabetes status will be determined once the underlying distribution and quality of the data are assessed. As quality of life is not measured within the trial or available in the preintervention administrative data, utility weights will be assigned to birth outcomes using relevant literature sources [48,49].

A cost-utility analysis will be undertaken with the primary analysis from the perspective of the health care system. This perspective is the most commonly used economic evaluation method in Australia for policy makers [50] and will allow comparisons across other sectors to identify the relative cost-effectiveness of the intervention for funding proposals. An incremental cost-effectiveness ratio (ICER) will be calculated using the following formula:

where *int* is the new intervention, *usual* represents usual care, and *QALY* stands for quality-adjusted life-year.

The model will include sensitivity analysis of key parameters, and outputs will include cost-effectiveness acceptability curves; these will display the probability of cost-effectiveness at varying thresholds of net monetary benefit.

#### Statistical Analysis

Primary (program implementation) outcomes (reach, uptake, and retention) will be reported descriptively and compared with the outcomes of a retrospective face-to-face comparison group. Where corresponding data are available for any secondary outcomes (such as GWG), results from the retrospective group will be compared with those of the prospective group. Chi-square and independent sample *t* tests will compare outcomes between retrospective and prospective groups. Analyses of secondary (program effectiveness) outcomes in the prospective group will be by mixed models, which will allow for repeated measures (baseline and follow-up) and include all participants with baseline data (including those with missing data at follow-up), with adjustment for predictors of dropouts to minimize selection bias. The relationship between intervention dose (number of calls received) and secondary behavioral and clinical outcomes will be examined. The optimal model will be selected using both indices of fit and model interpretability and parsimony. Outcomes will be reported as per protocol and intention-to-treat. Per protocol is defined as any participant who completed 4 or more telephone counseling sessions. Sensitivity of conclusions to missing data assumptions will be evaluated.

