## Methods

### Study Design

The LWdP program will use a type 2 effectiveness-implementation hybrid design [23] to compare prospectively gathered data on participants enrolled in the LWdP program with a retrospective comparison group who was referred to the dietitian for pregnancy weight management. The setting is a tertiary metropolitan hospital that delivers approximately 4500 babies per year and offers 8 different models of antenatal care for both high- and low-risk pregnancies, including general practitioner shared care. These models of antenatal care will be consistent across the retrospective (preimplementation) and prospective (postimplementation) study periods. The retrospective control group will comprise pregnant women referred for dietetic care in the 12 months prior to the study period who meet the inclusion criteria. The prospective group will be consenting participants in the LWdP program referred for dietetic care during the 12-month study period. The RE-AIM evaluation framework will be used to understand the following about the LWdP program: reach and adoption (the number and representativeness of service referrers and participants), implementation (number of referrals, consent rates, fidelity of delivery, program completion rates, and costs of delivery), and effectiveness (maternal and neonatal outcomes) [22]. Evaluating the maintenance domain will not be possible within the time frame of the study. Ethics approval was granted from the Royal Brisbane and Women’s Hospital Human Research Ethics Committee (HREC/17/QRBW/159).

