### Engagement Strategy

Staff will be engaged in the planning phase of LWdP program implementation to identify preferred referral processes for each of the hospital’s 8 different antenatal models of care. This will inform the introduction of an outpatient dietetic referral form for the LWdP program alongside other dietetic services at the facility and the inclusion of the LWdP program referral in paperwork completed during women’s initial booking-in appointment. A program website will be developed to facilitate an online referral pathway, allowing both self-referral and referral by external antenatal health care providers located in the community of women under their care. A consumer engagement survey will be undertaken to inform the flexible program delivery hours, education needs, and topics of interest. Staff from each antenatal model of care will be provided with regular in-services, and the hospital’s media and communications team will be engaged to help build publicity for the program by featuring consumer stories in local newsletters, social media accounts, and local general practitioner communications.

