## Results

The LWdP program commenced in February 2018. The prestudy period for retrospective data inclusion was from October 2016 to October 2017 and includes data from 49 women. The poststudy period for data collection commenced when the program was initiated in February 2018 and the last included participant for data analysis was enrolled in August 2019. A total of 152 women consented to have their data included in the poststudy period. Data collection of all variables was finalized in December 2020. Data cleaning has commenced and data analysis will be completed by June 2021.

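### The between-group comparison of GWG and other secondary outcomes is unadjusted, although the historical controls and the programme participants were assembled differently, so any difference mixes programme effect with case-mix

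*Protocol article*

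**What the plan says.** The Statistical Analysis section of the protocol article extends the group comparison to effectiveness outcomes: "Where corresponding data are available for any secondary outcomes (such as GWG), results from the retrospective group will be compared with those of the prospective" (that is, women enrolled in the programme). It then names the method, chi-square and independent-sample t: "tests will compare outcomes between retrospective and prospective groups".

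Two other statements come near to adjustment:
- Same section: "Analyses of secondary (program effectiveness) outcomes in the prospective group will be by mixed models", to be run "with adjustment for predictors of dropouts to minimize selection bias". These models are confined to one group.
- GWG section, on women who deliver before the 36-week appointment: "the last recorded weight will be used to estimate GWG and will be adjusted for in multiple variable analysis".

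On the make-up of the groups, Study Design defines the controls: "The retrospective control group will comprise pregnant women referred for dietetic care in the 12 months prior to the study period who meet the inclusion" (the list of entry conditions). Against them stand consenting programme participants. Screening and Consent records a consent waiver for the retrospective women. Engagement Strategy adds programme referral to the booking-in paperwork, staff in-services, publicity and a website "allowing both self-referral and referral by external antenatal health care providers". The Results section gives October 2016 to October 2017 for the retrospective data, which "includes data from 49 women", and 152 consenting women enrolled from February 2018 to August 2019.

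**The concern.** A two-sample test without covariates estimates a programme effect only if the two groups would have had similar outcomes without the programme. Nothing in this design secures that. The groups are not randomised, come from different years, reach the service by different routes and pass through different consent steps. The antenatal care models and the inclusion criteria are the only features said to be common to both.

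This is the only comparison with usual care that the article describes for GWG and pregnancy outcomes. If the two groups differ in prepregnancy BMI, age or parity, the plan as written would report that difference as a programme effect, or would let it hide one.

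**Working it through.** **1. Does any stated adjustment reach this comparison?**

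| Statement | Applies to | Adjusts for | Covers case-mix between groups? |
|---|---|---|---|
| Chi-square and t tests | Retrospective v prospective | Nothing named | No |
| Mixed models | Prospective group only, baseline to follow-up | Predictors of dropout | No |
| Multivariable analysis in the GWG section | GWG; contrast not stated | Use of the last recorded weight in early deliveries | No |

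**2. Is a case-mix difference plausible on the article's own account?**
- *Referral.* The Background says that fewer than 10% of eligible women were referred under the face-to-face model. The programme sets out to change this, so a change in who is referred should be expected.
- *Engagement.* Controls need only have been referred. Prospective women must take part and consent. Without a written form, two documented verbal consents are needed, the second at programme completion. This favours women who stay engaged.
- *Prognosis.* The article itself treats prepregnancy BMI as prognostic: the recommended gain ranges depend on it, and birth costs are to be stratified by it.

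**3. How much could it matter?** The article gives no power calculation, SD or baseline comparison, so there is no planned figure to reproduce. What follows is illustration. The group sizes are the article's. The shift sizes and the two-sided 5% level are assumptions.

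*Standard error of a mean difference, in SD units:* sqrt(1/49 + 1/152) = sqrt(0.02041 + 0.00658) = 0.164.

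*Continuous outcome, no programme effect, case-mix shift b (in SD).* False-positive rate = Φ(b/0.164 − 1.96) + Φ(−b/0.164 − 1.96):
- b = 0.1: 9%
- b = 0.2: 23%
- b = 0.3: 45%

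*Binary outcome, no programme effect.* Pooled two-proportion test, control risk 40% to 60% (the article's background range for excessive GWG), lower risk in the prospective group:
- 5-point shift: 9% to 10%
- 10-point shift: 23% to 26%
- 15-point shift: 45% to 52%

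*For scale.* The difference detectable with 80% power is (1.96 + 0.84) × 0.164 = 0.46 SD for a mean, and 20 to 23 points for a proportion.

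*What imbalance produces such shifts?* Bias = difference in prevalence × effect of the factor. A 20-point imbalance in a factor worth 20 to 30 points of excessive GWG gives 0.20 × 0.20 = 0.04 to 0.20 × 0.30 = 0.06, that is 4 to 6 points.

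**4. Does adjustment help?** A simulation of 4,000 replicates per setting used 49 v 152, no programme effect and one binary confounder. Its prevalence was 60% in controls and 20 to 30 points lower in participants, and its effect was 0.5 to 0.8 SD.
- Unadjusted t test: bias −0.10 to −0.24 SD, false-positive rate 9% to 29%.
- Regression on group and confounder: bias about 0, false-positive rate 4% to 6%.

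**The case against.** **The outcomes are secondary and the limitation is disclosed.** The primary service-level outcomes are mainly descriptive, and the Discussion concedes that a retrospective control limits interpretation compared with a randomised trial. Both points stand and lower the severity. But the Discussion offers no analytic remedy.

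**A multivariable GWG analysis is foreseen, and its covariates may be in a fuller plan.** This stands in part. It cannot be said that no multivariable GWG model is intended. But the article does not merely leave the between-group method open: it names unadjusted tests. The one factor in the GWG section does not concern case-mix, and nothing comparable is stated for pregnancy or neonatal outcomes.

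**The bias may be small beside sampling error.** At risks of 40% to 60%, the 95% confidence half-width is 1.96 × sqrt(p(1 − p)) × 0.164, about 16 points. A bias of 4 to 6 points is a quarter to a third of that. This is fair. The larger false-positive rates above need larger imbalances, which are assumed.

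**Some obvious covariates may be consequences of the programme.** Gestation at referral, weight gained by referral and referral route may all change because the programme alters when and how women are referred. Adjusting for them, or restricting to clinician-referred women, could remove part of the effect of implementing the service. This stands and limits the fix.

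A reader might also infer two further points that are not supported:
- *That chi-square is unreliable for rare outcomes with 49 controls.* Exact enumeration at 49 v 152 gives the uncorrected test a true size of 3.1% to 4.5% at risks of 2% to 10%. It is slightly conservative, not inflated. Fisher's exact test is more so, at 1.9% to 3.7%.
- *That this contrast feeds the incremental cost-effectiveness ratio.* The Economic Evaluation section describes a model with hospital birth costs and utility weights from the literature. It does not say that the unadjusted contrast is an input.

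**Conclusion.** The point holds for the secondary effectiveness outcomes compared between groups, and for those only. As written, the plan tests a non-randomised, historically controlled contrast without adjustment, while its GWG section refers to a multivariable analysis that its Statistical Analysis section does not describe.

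The size and direction of the bias are unknown. On assumed shifts of 5 to 10 points or 0.1 to 0.2 SD, the false-positive rate is about 9% to 26% instead of 5%. This should be corrected before the comparison is read as evidence of effectiveness. It is not a fatal fault, and it does not touch the descriptive reporting of the primary outcomes.

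**What to change.** Reconcile the GWG and Statistical Analysis sections, as follows:
- **Main between-group analysis of GWG and pregnancy outcomes:** a regression (linear for GWG; logistic or modified Poisson for binary outcomes) or a propensity- or overlap-weighted comparison. Adjust for a short prespecified list of routinely recorded pre-programme characteristics: prepregnancy BMI, age and parity.
- **Last recorded weight:** state that the adjustment for early deliveries belongs to this GWG model, if that is the intention.
- **Sensitivity analyses only:** adjustment for gestation at referral and weight gain to referral, and restriction to clinician-referred women, with the reason given.
- **Chi-square and t tests:** keep them as descriptive.

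The cost is a change of analysis wording and possibly some record extraction. The article says that pregnancy weights have been routine since 2015, but it does not confirm that every covariate is available for controls. Missing values may need imputation. With 49 controls only a few covariates can be supported. Adjustment removes measured confounding only and will not fully correct selection through consent, so the limitation in the Discussion should stay.

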### Participants and Referral Pathways

All women aged ≥16 years without pre-exiting diabetes with a prepregnancy BMI >25 kg/m^2^ who are referred for dietetic weight management care during the study period will be eligible for participation. For the purpose of this evaluation, participants must be able to speak and read English sufficiently to allow program participation. Those women who do not meet these criteria will be provided with appropriate face-to-face dietetic care and not participate in this evaluation. Women will be referred into the program by their treating health care provider if they meet these criteria. Alternatively, women meeting these criteria will be able to self-refer into the program through a dedicated program website. Women who are engaged in the program who develop gestational diabetes will be provided the option to remain in the program or withdraw to the hospital’s gestational diabetes model of care.

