Women referred to the program will be eligible for up to 10 telephone coaching calls over the course of their pregnancy that will usually span a period of 6 months (1 call each week for 1 month, then 1 call every 2 weeks for the next month, then 1 call per month for the next 4 months) and will also receive a participant workbook (Textbox 1). The initial telephone call will be approximately 60 minutes in duration, with subsequent calls lasting approximately 30 minutes, with an emphasis on motivational interviewing [26] and tailored health behavior coaching [27]. The program has been adapted for pregnancy from the Healthy Living after Cancer program [28] and informed by previous formative work with women participating in the New Beginnings Healthy Mothers and Babies study at the same institution [1,20,29,30]. Specifically, the program will target behavioral constructs and consumer experiences gained from prior research with the study population [1,20,29,30]. The intervention is grounded in the social cognitive theory constructs of self-efficacy, social support, and outcome expectancies [31] and emphasizes developing skills using behavior change strategies—goal setting, self-monitoring, identifying potential barriers and problem solving, identifying social support, stimulus control, mindful eating, positive self-talk, and self-reward. The protocol for each call includes an assessment of progress, problem solving, advice/education, collaborative goal setting/goal progression, and development/revision of a behavior-specific action plan. The program topics have been mapped to the refined taxonomy of behavior change techniques [32], as shown in Multimedia Appendix 1.

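### Gestational diabetes can cut the number of calls received, so relating total calls to gestational diabetes can show a benefit when there is none

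*Protocol article*

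**What the plan says.** Statistical Analysis defines the exposure as a plain count of calls: "The relationship between intervention dose (number of calls received) and secondary behavioral and clinical outcomes will be examined". It gives no cut-off date and no scaling to the number of calls a woman could have had. Table 1 places GDM under effectiveness, among the secondary delivery and pregnancy outcomes.

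Under Participants and Referral Pathways, women who develop GDM while in the program "will be provided the option to remain in the program or withdraw" to the hospital's own GDM model of care. The LWdP Program section offers "up to 10 telephone coaching calls over the course of their pregnancy that will usually span a period of 6 months", spaced as "1 call each week for 1 month, then 1 call every 2 weeks for the next month, then 1 call per month" for the remaining four months.

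On analysis sets, Statistical Analysis says: "Outcomes will be reported as per protocol and intention-to-treat", and "Per protocol is defined as any participant who completed 4 or more telephone counseling sessions". Between-group comparisons are unadjusted: chi-square tests and "independent sample *t* tests will compare outcomes between retrospective and prospective groups". The mixed models for the prospective group are planned "with adjustment for predictors of dropouts to minimize selection bias".

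**The concern.** A dose-response analysis is informative only if the dose is settled before the outcome, or at least is not altered by it. Here a woman diagnosed with GDM may stop receiving calls because of the diagnosis. She then appears in the data as a low-dose woman with GDM, although the low dose came second. This is reverse causation built in by the plan's own definitions, and it favours the program.

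The Discussion says the results are meant to inform funders, policy makers and decisions on scaling up. A spurious gradient of GDM on call number could be read as evidence that more calls prevent GDM.

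There is a lesser, related point. The per-protocol set is selected after baseline by attendance at telephone sessions. The retrospective group had unstructured face-to-face care, and no corresponding attendance threshold is defined for it.

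**Working it through.** **1. The plan's own figure.** Four weekly, two two-weekly and four monthly calls give 4 + 2 + 4 = 10, which matches the stated maximum. Taking a month as 4 weeks, the calls fall at weeks 0, 1, 2, 3, 5, 7, 11, 15, 19 and 23 after entry.

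**2. What leaving on GDM does to the count.** The article gives no time of diagnosis, so take 27 weeks as an example.
- Entry at 13 weeks: calls at 13, 14, 15, 16, 18, 20 and 24 weeks come before diagnosis, which is 7. A woman who stays can have 10 by 36 weeks (13 + 23 = 36). The loss is 3.
- Entry at 20 weeks: calls at 20, 21, 22, 23, 25 and 27 weeks, which is 6. A woman who stays can have 9 by 40 weeks (20 + 19 = 39). The loss is again 3.

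**3. Odds ratio under no effect.** Assumptions not in the article: GDM 20%, diagnosed at 26 to 28 weeks; entry at 8 to 20 weeks; 25% to 75% of women with GDM leave; other dropout 4% to 15% per call and unrelated to outcome. Logistic regression of GDM on total calls gives an odds ratio per call between 0.84 (75% leave, 4% dropout) and 0.98 (25% leave, 15% dropout). If half leave, it is 0.89 to 0.96. The true value is 1.

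**4. False-positive rate at the actual size.** The Results section gives 152 women in the prospective group. Assumptions: entry at 10 to 20 weeks, delivery at 39 weeks (SD 2), diagnosis at 24 to 28 weeks, other dropout 8% per call, two-sided test at 5%, no program effect.

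| GDM frequency | 25% leave | 50% leave | 75% leave |
|---|---|---|---|
| 10% | 6% | within the range | 27% |
| 20% | 9% | 23% | 52% |
| 30% | 11% | 32% | 65% |

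Women with GDM average about 0.4, 0.8 and 1.2 fewer calls as the share leaving goes from 25% to 50% to 75%. If none leave, the rate is about 5% to 6%, so the excess comes from leaving on GDM.

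**5. Does a landmark remove it?** With dose taken as calls received by 24 weeks and adjustment for gestation at entry, the false-positive rate is 4.5% (GDM 20%, half leave) and 5.1% (GDM 30%, 75% leave), against 23% and 65% with total calls. The odds ratio in step 3 returns to 1.00.

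Allowing for entry matters because the schedule permits 7 calls by 24 weeks for entry at 13 weeks, but only 4 for entry at 20 weeks.

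**6. Early delivery and late entry alone.** Under no effect, these give a false-positive rate of 5% to 8% for calls against birth weight, with a correlation of at most about 0.04. Late calls are monthly, so early delivery removes only one or two.

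**7. Per-protocol against all 49 controls, for gestational weight gain (GWG).** An SD of 6 kg is assumed. If persistence with calls is unrelated to prognosis, the false-positive rate is about 5%. With a moderate link there is a spurious difference of 0.25 to 0.85 kg and a rate of up to 11%. Intention-to-treat stays at 4% to 6%.

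**The case against.** The strongest reply is that this is one exploratory sentence about secondary outcomes in a study whose primary outcomes are implementation measures. The sentence promises to examine a relationship, not to estimate a causal effect. The plan also reports intention-to-treat, includes all prospective participants with baseline data in the mixed models, adjusts for predictors of dropout and tests sensitivity to missing-data assumptions. This limits the weight of the point but does not answer it. The dropout adjustment is stated for repeated-measures models, whereas GDM occurs once, and no baseline covariate can remove truncation caused by the outcome itself.

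Three stronger readings are tempting, and the article does not support them.

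- A reader might infer that the dose and per-protocol analyses must both show associations under no effect. They can, but need not. If no one leaves on GDM, the dose analysis for GDM is close to its nominal error rate. If persistence is not prognostic, so is the per-protocol comparison. The fourth call falls about 3 weeks after entry. With entry before 20 weeks, as in the Abstract, the per-protocol set is normally settled by about 23 weeks, before the diagnosis times assumed here. In simulation, GDM among women with four or more calls stayed at the assumed 20%.
- A reader might infer that birth weight and GWG will track call number through length of gestation. Step 6 shows little of this for birth weight. The GWG section fixes the measure at 36 weeks, with adjustment for women who deliver before that visit. Gestation at entry is a baseline variable that ordinary adjustment can handle.
- A reader might fault the article for not saying which analysis set leads. For secondary outcomes that can be left to the statistical analysis plan. Nor does the article say outright that the per-protocol set will be tested against the retrospective group.

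**Conclusion.** The point holds for GDM. The article defines dose as calls received, relates it to clinical outcomes that include GDM, and allows women to leave on GDM, so total calls cannot be interpreted as a cause of GDM. Under the assumptions above with GDM at 20%, the bias is an odds ratio of about 0.84 to 0.98 per call and a false-positive rate of 9% to 52% at 152 women. GDM frequency, the share leaving, other dropout and timing of diagnosis are all assumed. With few women leaving, the problem is small.

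The per-protocol point is secondary and conditional. The set is a post-baseline selection with no control counterpart, and a comparison with the retrospective group can mislead if women who persist have a different prognosis. It is a matter of labelling. The change is worth making because it is cheap; the primary outcomes are not affected.

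**What to change.** Amend the dose sentence in Statistical Analysis as follows.

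- **GDM:** count only calls received before diagnosis or screening. Alternatively, count calls up to a fixed landmark before it, among women enrolled by then and still GDM-free.
- **GWG:** count only calls received before the weight used in the calculation.
- **Both:** adjust for gestational age at enrolment, or divide calls received by calls scheduled to that point.
- **Per-protocol:** label any comparison of this set with the retrospective group as supportive.

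Each telephone session is already to be recorded in REDCap, so no new data collection should be needed. The price is less variation in dose and hence less precision; with a landmark, women who enrol or develop GDM before it is reached drop out of that one analysis in the first case only if enrolment comes after the landmark, and in the second case always. Women's option to stay or leave after a GDM diagnosis is untouched.
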